## Abstract

**Background:**

Asylum seekers who arrive in their host countries worldwide present with an alarming burden of trauma and distress. Related mental ill health is a matter of concern and hinders the mobilisation of resources necessary for successful social adaptation and integration into host communities, creating a vicious cycle. Although effective treatment is available, services are only accessible when conditions become chronic and/or life-threatening. To overcome the manifold barriers to care, we aim to implement a screen-to-counsel, stepped-care trauma rehabilitation programme for asylum seekers upon arrival in Germany. Individuals are invited to a personal interview at the end of which they are offered a specific intervention, depending on the severity of their symptoms and level of support needed: [s1] watchful waiting; [s2] Narrative Trauma Work (NAT), adapted from Narrative Exposure Therapy (NET; Schauer, Neuner, Elbert, 2025), delivered by peer migrant counsellors; or [s3] treatment by a licensed clinical psychological expert. This study is initiated to assess the effectiveness of the NAT intervention and the sustainability of the overall program within in the German health service setting.

**Methods:**

To assess the effect of NAT, we will apply a quasi-experimental parallel group study with a natural waiting list control group (regression discontinuity design). Follow-up assessments will be conducted continuously up to 12 months later, in person and online. The outcomes of the study will include symptoms of depression, anxiety and posttraumatic stress, using the Refugee Health Screener (RHS-15, primary outcome). The study will also assess social and economic integration, and resilience, as well as successful application of the NAT counselling intervention, amongst other measures. Cost-effectiveness and sustainability will be assessed for the overall programme. Sustainability will be measured on the basis of counsellor participation and satisfaction using a mixed methods approach. The study will be conducted at various selected sites in southwest Germany.

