A special role within the mainstream psychotherapy approaches for refugees is played by Narrative Exposure Therapy (NET) [21, 65, 66]. About 25 years ago, in the context of organized violence, war and torture in Yugoslavia, Northern Uganda and Sri Lanka, a group of psychologists and researchers have developed NET [67]. The approach was grounded in culturally sensitive principles and universal neural mechanisms applicable to heterogeneous populations of refugees (and non-refugees), prioritising survivors' recovery needs and addressing multiple traumatisation [68–70]. With this approach, the developers broke with the then-prevailing taboo surrounding discussion of traumatic events, alongside prolonged exposure [71] and gave rise to a new era of trauma rehabilitation by giving victims a voice through testimony [68]. To allow for an efficient implementation in war-torn and resource-poor regions, NET is manualised, brief, and open access. Implementation by local counsellors without academic graduation in (clinical) psychology has become a pragmatic and successful *modus operandi* [72–77], including NET training-of-trainers schemes [77, 78]. Moreover, NET stands out for its ability to address severe and multiple traumatization across lifetime. While NET has been refined and adapted over the past decades, it has kept its outstanding procedural core structure and features, especially the theoretical framework which has been validated by numerous independent studies across various fields of psychotraumatology [14, 79–81]. Today, NET is considered one of the gold standard treatments of PTSD. The manual was translated in 12 languages and is used worldwide, universal applicability also allowed for the treatment if survivors in at risk populations, including survivors who are homeless or vulnerably housed [82, 83], who live in contexts of ongoing violence [84–87], or in psychiatric wards [88]. Clinical studies and randomised control trials (RCTs) with a broad population have confirmed significant treatment effects on posttraumatic stress symptom severity [89–93] as well as related problems such as depression [77, 94–96], borderline symptoms [94, 97, 98], somatization [99], physical health [70], pain symptoms [100], quality of life [101], guilt [72], shutdown dissociation and dissociative identity disorder [102, 103], aggression [86, 104], drug dependence [77], psychosis [105–107], disability [108], social dysfunction [86, 88, 104], chronic mental disorders [88, 109] and negative intergenerational effects [110]. Evaluations have further corroborated the benefits of NET by determining mechanisms of treatment effects on symptoms, such as improved top-down frontal cortical regulation of emotions and behaviour [111], improved immunological responses [99], and multiple epigenetic outcomes [112]. The benefits of NET not only appear shortly following completion, but also persist over time [90, 113]. The long-term effectiveness of NET deserves particular emphasis, and many (network) meta-analyses and reviews fail to capture this important aspect. NET was adapted for the special needs of children and adolescents [114, 115], perpetrators [84, 86, 116], communities [85, 117, 118] and online delivery [119, 120], and it is applicable and effective in a wide variety of samples without the need for further adaptation (see Box 1).

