## Trial design

The present study employs a naturalistic parallel groups design, integrating a regression discontinuity statistical approach for quasi-randomisation with a classical longitudinal design. The resulting pattern of evidence will indicate the sustainability, cost-effectiveness and effectiveness of the programme while we ensure that all study participants receive evidence-based treatment.

Assessments include an in-person baseline screening, monthly online or assisted self-assessments (hereafter: well-being monitor), and an in-person follow-up at 6–9 months post-baseline. Given the central role of the peer counsellors in the programme, we will assess their training and supervision in terms of acceptability, efficiency and motivations, through focus group discussions and survey-based evaluations. These evaluations will take place before the counsellors begin their active work and after they have completed a substantial number of NAT steps (screenings, referrals, checklist intakes, lifeline sessions and narrative event-telling sessions).

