## Interventions

### Explanation for the choice of comparators

In this naturalistic study, the following potential comparators to NAT (treatment condition) evolve: (1) NAT clients awaiting treatment; (2) clients with clinically relevant symptoms who are either (2a) waiting for psychotherapy or (2b) receiving psychotherapy; (3) clients without symptoms waiting for follow-up; and (4) clients before vs. after NAT (individual trajectories of symptom development, Table 1).

**Table 1 Tab1:** Constellation of comparators

Treatment condition	Control condition	Limitation	Mitigation
[1] NAT	Awaiting NAT (RHS 13–36)	Reduced follow-up time points for those who wait for treatment; unknown N	-
[2] NAT	[2a] PT waiting [2b] PT receiving	Clients might still wait but may have started, or already finished PT; higher symptoms of the control group at baseline	Statistical control for the number of treatment sessions, use of the RDD
[3] NAT	Watchful waiting (RHS < 13)	Lower symptoms of the control group at baseline, low symptom levels generally	Evaluate number of clients who present with improving vs. deteriorating symptoms rather than
[4] After NAT	Before NAT	Within subject comparison; potential confounding factors	-

Note: RHS-15 = 15 item Refugee Health Screener with a sum score indicating symptom severity; PT = Psychotherapeutic sessions provided by a licensed Psychotherapist. Threshold to clinical relevance is suggested for ≥37. Watchful waiting is indicated for clients with ≤12 points

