### Outcomes

Outcomes of interest include the participants´ somatic and psychological symptoms, social integration, mental health literacy of the client, general life satisfaction, and post-migration stressors. Baseline and a follow-up assessment will be administered by NAT counsellors in face-to-face interviews and will assess psychological symptoms and social integration. Additional instruments are listed in Table 3 will be administered online.

**Table 3 Tab3:** List of instruments of the well-being monitor

Outcome	Measure	Author	Admin.
Somatic symptoms	Somatic Symptom Scale-8 (SSS8)	Gierk et al. [129]	online
Psychological symptoms	Refugee Health Screener (RHS-15)	Hollifield et al. [130]	both
Life satisfaction	Satisfaction with Life Scale (SWLS)	Diener et al. [131]	online
Social networks	Lubben Social Network Scale (LSNS-6)	Lubben [132]	online
Social and economic integration	Immigration Policy Lab Integration Index (IPL-12)	Harder et al. [133]	both
Mental Health literacy Scale	Mental Health Literacy Scale (MHLS)	O’Connor et al. [134]	online
Resilience	Brief Resilience Scale (BRS)	Smith et al. [135]	online
Self-efficacy	General Self-Efficacy Short Scale-3 (GSE-3)	Doll et al. [136]	online
Food insecurity	Food Insecurity Experience Scale (FIES)	Cafiero et al. [137]	online
Food environment	Access to preferred food types	Adapted from Hadley et al. [138]	online
Aggression	Adapted version of the event scale of the appetitive aggression scale	Weierstall et al. [139]	both
Note: Both = to face-to-face interviews and online			

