#### Assessment (refugees)

Data collection from refugees begins with a face-to-face interview conducted by one of the NAT counsellors (see Sect. Intervention description) and continues with 10-minute monthly online assessments (Well-being Monitor). Approximately 6 to 9 months after the initial screening, refugees will be invited to a face-to-face follow-up interview.

At the start of the face-to-face baseline interview, we will ask for demographic information, screen for trauma related symptoms, and collect information on social and economic integration. The follow-up interview after 6–9 months will re-assess levels of psychological distress and integration.

The 15-item Refugee Health Screener [123] will be used to assess the severity of trauma related reactions. The RHS was adapted from validated instruments for depression, anxiety and PTSD to screen for trauma related reactions in refugee populations. Each item is rated on a scale from 0 (not applicable at all) to 4 (extremely) and a total score of items 1–13 indicates the severity of symptoms (0–52) and the intensity of treatment required. Items ask for instance for nightmares, loss of interest or other trauma related symptoms. Items 14 and 15 are taken into account in a qualitative way. The RHS was recently validated with refugees in the German context [124]. Kaltenbach et al. [124] found high sensitivity and good feasibility, reliability and validity for both the self-rating and interview versions. Strong psychometric properties of the RHS were also found in other studies in Germany [147, 148] and elsewhere [149, 150].

An adapted version of the Appetitive Aggression Scale [139] for refugees will be used to assess aggression. The AAS is a 15 item semi structured interview that measures appetitive aggression according to the extent of agreement to statements, on a scale ranging from 0 (disagree) to 4 (agree) for each item. A total sum score will be used to measure severity of aggression (max 60).

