Generalised linear mixed models (GLMM) with subgroups defined by the RDD will be used in addition and allow for integration of multiple follow-ups, if robust (*N*_min_ is sufficient to detect a small to moderate effect). Thus, to test the efficacy of NAT in comparison to our controls in regards to primary and secondary outcomes, we plan to use separate generalised linear mixed models (GLMMs) in R. To account for non-independence of measurements, we will include individuals as a random part of the models. To account for repeated measures, we will control the within-group variance for the effect of time, i.e. baseline and 3 and 6-month follow-ups, according to A Field, Z Field and J Miles [179]. To estimate the significance of the fixed terms, we plan to fit the models using maximum likelihood (ML), and compare models with and without each fixed term using likelihood-ratio tests [180]. In cases where the interaction term is significant, we will use post hoc Tukey tests using the R package emmeans [181] to assess which contrasts differ significantly. To correct for multiple comparisons controlling the false discovery rate, we will further adjust P-values accordingly [182].

Additionally, effect sizes will be estimated by calculating Cohen’s d [183] for within and between group differences following W Lenhard and A Lenhard [184]. Clinically significant change will be calculated using the reliable change index, following NS Jacobson, LJ Roberts, SB Berns and JB McGlinchey [185].

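### RHS-15 is collected monthly, but the only repeated-measures model is defined on baseline, month 3 and month 6, so most primary-outcome readings have no named analysis and short-waiting controls have no untreated follow-up in it

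*Protocol article*

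**What the plan says.** **Collection.** The abstract (Methods) gives the overall length: "Follow-up assessments will be conducted continuously up to 12 months later, in person and online". The Trial design section lists, after the baseline screening, "monthly online or assisted self-assessments (hereafter: well-being monitor), and an in-person follow-up at 6–9 months post-baseline". The section Assessment (refugees) repeats that data collection "continues with 10-minute monthly online assessments (Well-being Monitor" and names no last month. Table 3 marks RHS-15 with the administration code explained as "Note: Both = to face-to-face interviews and online", so the primary outcome is part of every monthly survey as well as the interviews.

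**Analysis.** Under Statistical methods, item [3], the GLMM is the only model for repeated measures. It is additional to the regression discontinuity analysis and conditional on sufficient numbers. Its time factor is spelled out: "we will control the within-group variance for the effect of time, i.e. baseline and 3 and 6-month follow-ups". In Table 4, hypotheses 2a and 2b are read at 6–9 months, and hypothesis 3 names no month. The regression discontinuity text speaks only of a follow-up value.

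**Waiting controls.** Row [1] of Table 1 compares NAT with clients awaiting NAT. It lists as a limitation "Reduced follow-up time points for those who wait for treatment; unknown N" and gives a dash under mitigation.

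**The concern.** The article itself states both the collection schedule and the model's time points, and the two do not match. Read literally, the GLMM omits months 1, 2, 4 and 5, everything after month 6, and any face-to-face follow-up held in months 7–9.

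Three things are at stake. The first is the waiting-list comparison, the control group named in the abstract. Waiting clients go on to receive NAT, so their untreated readings come early, and months 1 and 2 are the early follow-up readings that the model does not name. The second is some precision on the primary outcome, in a study whose Limitations section says that group sizes cannot be predicted. The third is clarity about how long the follow-up is and what the late readings are for.

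**Working it through.** The plan prints no figure for this point, so there is nothing to reproduce. The check is a count, a reading of the waiting-list contrast, and a bound on the precision.

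**1. Count of RHS readings per client.** Taking the abstract's 12 months with the monthly schedule gives 12 monthly readings plus 1 interview, or 13 after baseline.
- Named in the GLMM: months 3 and 6, so 2 of 12 monthly readings (17%). Unnamed: 10 of 12 (83%).
- Hypotheses 2a and 2b need one classification per client at 6–9 months. Counting the interview for that, at most 3 of 13 readings (23%) have a named use and 10 of 13 (77%) have none.
- The 12 months appear only in the abstract. If the monthly series stopped at month 9, 7 of 9 (78%) would be unnamed. If it stopped at month 6, 4 of 6 (67%) would be unnamed. Most readings are unnamed in each case.
- Readings in months 10–12 (3 of 12, 25%) lie later than any time that an analysis names.

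**2. Waiting-list contrast.** Let a client start NAT *w* months after screening. The client's untreated follow-ups are those before *w*. If *w* < 3, neither month 3 nor month 6 is untreated, so the client gives the GLMM no untreated follow-up at all. Months 1 and 2 can supply one or two. The document gives no waiting times, so the share of clients affected cannot be computed.

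**3. Bound on precision.** For the baseline-adjusted mean of *k* follow-ups with equal correlation ρ, the variance in units of the outcome variance is

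V(k) = (1 + (k − 1)ρ)/k − ρ².

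The correlation is not in the document. ρ = 0.4 to 0.8 is assumed.

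| ρ | V(2), months 3 and 6 | V(6), months 1–6 | Reduction |
|---|---|---|---|
| 0.4 | 0.540 | 0.340 | 37% |
| 0.6 | 0.440 | 0.307 | 30% |
| 0.8 | 0.260 | 0.193 | 26% |

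**4. Why this is only an upper bound.** The table assumes that every form is returned and that the effect is fully present from month 1. NAT is delivered in steps, so suppose instead that the effect rises linearly to its full size at month 3. The months 1–6 mean then captures (1/3 + 2/3 + 1 + 1 + 1 + 1)/6 = 0.833 of it. At ρ = 0.6 the standard error ratio is √(0.307/0.440) = 0.835. The relative signal-to-noise is 0.833/0.835 = 0.998, so the gain is gone. With no effect at month 1 and half at month 2, the captured share is 4.5/6 = 0.75 and the ratio is 0.75/0.835 = 0.90, a loss. An average over months 1–6 would therefore change what is estimated and need not be sharper.

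**The case against.** The best defence is that the text is loose rather than restrictive. The same paragraph says that the GLMM can integrate several follow-ups. The missing-data section prefers mixed models because they keep observations, and row [4] of Table 1 plans individual symptom trajectories. Which readings enter a mixed model is often settled in an analysis plan, which is not shown.

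Part of this stands. A reader might infer that the remaining RHS data will be discarded. The document does not say so; it only leaves those readings without a named analysis. But months 3 and 6 are already several follow-ups, so the general remark does not override an explicit list introduced by i.e. The article chose to state the time points, and they conflict with its own schedule.

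Four other inferences are tempting and go too far:
- That no test uses data after month 9. Hypothesis 3 and the regression discontinuity outcome give no month, so the exact statement is that none names a later one.
- That a promised test of lasting effect is missing. No objective or hypothesis promises one. The sentence "The long-term effectiveness of NET deserves particular emphasis" is background on the published literature.
- That payments for primary-outcome data are wasted. The 5€ covers a survey with many instruments, and the monitor also serves the programme.
- That a months 7–12 contrast between NAT and waiting clients would show durability. By then waiting clients may have had NAT, and treated would be compared with treated.

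**Conclusion.** The mismatch is real and worth correcting. As written, the GLMM leaves most scheduled RHS readings without a named analysis (10 of 12 monthly, or 7 of 9 or 4 of 6 under shorter schedules). It also has no place for an interview in months 7–9. The consequence that matters most is for the waiting-list comparator, where the omitted month 1 and 2 scores could partly repair a limitation that Table 1 leaves without mitigation. How many clients this concerns depends on waiting times that are not given.

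The precision argument is secondary. A saving of 26–37% of the variance is an upper bound under assumed equal correlations of 0.4–0.8, full return and a constant effect. It can be nil if the effect builds up over the first months. The 12-month length rests on the abstract alone. This is an inexpensive improvement to the plan and does not show that the main analysis is invalid.

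**What to change.** In the GLMM paragraph of Statistical methods, item [3]:

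1. Replace the list of baseline, 3 and 6 months by all collected RHS-15 readings, monthly and interview, with actual time since screening as the time variable.
2. Code NAT status as time-varying, so that a waiting client counts as untreated only until starting NAT.
3. State the time at which the treatment contrast is read, consistent with the 6–9 month hypotheses, and do not use an average over months 1–6. Treat later months as descriptive or secondary.
4. Reconcile the abstract, the Trial design section and the GLMM paragraph on the length of follow-up, giving the last month of the monthly series.

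If a precision gain is quoted, give it as an upper bound with its assumptions. No new data are needed. The cost is a change of wording and slightly more modelling work. Time-varying coding corrects the labelling of waiting clients. It does not make the start of NAT random, so the caution already in the Limitations section still applies.

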**Discussion:**

This study addresses a crucial gap in mental health care provision and integration support for refugees and strategic decisions for its implementation. Moreover, the programme builds on the work and evidence for trauma-focused treatment in refugee samples in low-income countries, but also from internally displaced persons and trauma-exposed individuals in post-conflict settings.

**Trial registration:**

ClinicalTrials.gov Identifier: DRKS00033410, January 29, 2024.

**Trial status:**

Protocol version: 1.0, Dec 13, 2024; Planned first recruitment: Apr 1^st^, 2024; Planned completion: unspecified.

**Supplementary Information:**

The online version contains supplementary material available at 10.1186/s12913-026-14071-7.

## Background and rationale

In the last years, forced displacement has affected an unprecedented number of people around the world. According to the United Nations High Commissioner for Refugees [1], a total of 108.4 million individuals were forced to leave their homes and resettle in 2022. Mid-2024 the organisation counted 122.6 million, an increase of > 8% per year, of which 54.3 million sought refuge in another country [1]. This increase is fuelled by intensifying waves of conflicts alongside poverty and the consequences of climate change [2]. Despite its relatively small size, Germany ranks fourth amongst the host countries with around 2.1 million refugees. Germany experienced a 28% increase in asylum applications from 2021 to 2022, and 35% increase from 2022 to 2023 [3], with the majority of refugees coming from Syria (31.2%), Turkey (19.1%) and Afghanistan (14.3%) [1]. A critical barrier to successfully manage and integrate these individuals is the high level of trauma exposure and the related mental consequences that manifest at individual levels and significantly impact community and societal dynamics.

### Trauma exposure and mental sequelae in refugee populations

For refugees, the months-long journey to Europe, depending on traffickers and the benevolence of strangers, is marked by an increased risk of victimisation as well as perpetration of violence. Typically, forced migration is preceded by periods of suffering and deprivation due to war, conflict, torture, childhood adversity, gender-based violence, and/or natural disasters. Numerous studies demonstrate the high trauma load in this population [4–9]. Moreover, arrival in the host country is associated with multiple burdens such as cultural (mis)understandings, loss of role, status and income, family, friends and more together with the ongoing insecurity during the asylum process. Given the insecurity and absence of formal protection, it is no surprise that violent offending is also reported [4, 5]. Such cumulative exposure to life threats and deprivation as well as the perpetration of violence have a profound and lasting impact on the mental health of individuals [10, 11]. Hereby, the pathological memory formation is one of the key drivers of symptom trajectories that lead to clinically relevant suffering [12].

*Trauma memory.* During violent, potentially traumatic and life-threatening experiences, the process of storing and later retrieval of information is different from everyday life events: Emotional valence (negative/positive), interoceptive arousal, sensory input, and cognitions (implicit information) are stored in a way that they are very easy to recall but with deficient integration of spatiotemporal information [10, 13–15]. When encountering further threats, the individual’s reaction will follow familiar responses from the past and thus maximize survival chances [16]. However, as threats and triggers prevail, the memory may develop its own intrinsic dynamic and form a highly individualized, idiosyncratic neural network [17]. As a result of this, changes that are initially adaptive in a threatening situation, may result in psychopathological conditions, such as uncontrollable re-experiencing of implicit trauma memory components, compulsive avoidance or approach of reminders, changes in mood and cognition, hyperarousal, and aggression. When violent offending occurred alongside with victimization, the memories of those separate events are not stored together in a homogenous neural network of violence [13, 18, 19]. Namely, violent offending can be perceived as a fascinating and lustful experience [18]. Distinguished by the negative or positive valence experienced at the time of the event, two distinct associative memory networks are formed: a positive memory “hunting” network for perpetration and a negative “fear” network for victimization. Negatively experienced traumatic events and positively experienced perpetrated events are opposing but share salient commonalities (see Fig. 1; e.g., seeing blood or heart pounding). The psychophysiological responses that occur during both event types are similarly involuntary and innate [20]. Sensorial cues, like hearing screams or seeing blood, and interoceptive cues, such as rapid heart rate or respiration, are common in both victimization and perpetration experiences and interconnect the two networks. The higher the rate of exposure to such events, the more likely for their associative memories to be disconnected from their temporal and spatial contexts. Mnesic defragmentation occurs: the “what” is remembered, but the “when” and “where” are detached [10, 15, 21]. The aforementioned shared cues are distributed differently across the fear and hunting networks, depending on which network is more strongly reinforced and how. Specifically, negative reinforcement - where using sensorial or interoceptive cues in the hunting network of perpetrated events diminishes temporarily potential triggers for the fear network. For example, individuals with higher levels of appetitive aggression may be less likely to develop PTSD due to this effect (e.g. [22, 23]). The hunting network can also experience positive reinforcement due to the vinherent and intrinsic rewarding properties of violence [18, 24, 25].
